## Abstract

**Background:**

Almost 90% of cancer patients suffer from symptoms of fatigue during treatment. Supporting treatments are increasingly used to alleviate the burden of fatigue. This study examines the short-term and long-term effects of yoga on fatigue and the effect of weekly reminder e-mails on exercise frequency and fatigue symptoms.

**Methods:**

The aim of the first part of the study will evaluate the effectiveness of yoga for cancer patients with mixed diagnoses reporting fatigue. We will randomly allocate 128 patients to an intervention group (*N* = 64) receiving yoga and a wait-list control group (*N* = 64) receiving yoga 9 weeks later. The yoga therapy will be performed in weekly sessions of 60 min each for 8 weeks. The primary outcome will be self-reported fatigue symptoms. In the second part of the study, the effectiveness of reminder e-mails with regard to the exercise frequency and self-reported fatigue symptoms will be evaluated. A randomized allocated group of the participants (“email”) receives weekly reminder e-mails, the other group does not. Data will be assessed using questionnaires the beginning and after yoga therapy as well as after 6 months.

**Discussion:**

Support of patients suffering from fatigue is an important goal in cancer patients care. If yoga therapy will reduce fatigue, this type of therapy may be introduced into routine practice. If the reminder e-mails prove to be helpful, new offers for patients may also develop from this.

**Trial registration:**

German Clincial Trials Register (DRKS00016034, 12/2018), retrospectively registered.

## Background

Cancer-related fatigue (CrF) is the most common symptom of cancer treatment. Up to 90% of oncological patients suffer from fatigue during treatment [1, 2]. Both physiological and psychosocial factors play an important role in the development of fatigue. Often, however, no specific cause can be identified and therefore no specific treatment can be offered. In these cases, additional support services should be provided to help patients to cope with symptoms of fatigue. These range from drug treatment approaches psychosocial counseling, psychoeducation, exercise training to so-called mind-body interventions [2].

CrF is characterized by an intense and chronic sense of tiredness and exhaustion that is not associated with previous stress and cannot completely be relieved by rest. This tiredness can be found on three levels: physical, emotional and cognitive. In order to manage the fatigue symptoms on all three levels, results of meta-analyses support a multimodal approach of cognitive, physical and emotional aspects to symptom relief [3], for example consisting of psychoeducation and mind-body intervention. Few findings on the efficacy of psychoeducative interventions covering cognitive and emotional aspects and behavioral techniques on fatigue symptoms in cancer patients exist [4–6]. With regard to mind-body interventions (physical and emotional aspects), there are predominantly findings that speak for their efficacy in fatigue. The term “mind-body intervention” refers to interventions that aim to strengthen self-care through active and health-promoting strategies. With regard to fatigue, the focus here is mostly on mindfulness-based procedures, meditations as well as Yoga or QiGong. A meta-analysis reports a moderate effect of mind-body interventions on fatigue symptoms [7]. Both the ‘Mindfulness-Based Stress Reduction Program’ (MBSR) by John Kabat-Zinn [8–10] and yoga interventions [11–14] or Pranayama [15] help reducing fatigue. Even compared to a supportive or psychoeducative group of patients with fatigue, yoga therapy showed significant effects [16]. However, there are also contradictory findings that do not support significant differences in fatigue symptoms through yoga intervention compared to a control group [17–19].

Follow-up findings for mind-body interventions dealing with fatigue vary widely. While some randomized controlled trials (RCT) show significant effects in fatigue following a mind-body intervention, but no longer after 3 months [12, 20], others found no effects immediately after an intervention, but 3 months later [21]. Lengacher et al. [22] showed significant reduction of fatigue compared to a CG after the intervention and also in a catamnesis 6 weeks later [22]. An observational study showed significant long-term effects of mind-body intervention regarding depression and general mood after 1 year, but no long term effects regarding fatigue [23].

The yoga therapy intervention we used in our study was already evaluated in previous studies. Using a randomized controlled design, Lundt et al. [24] showed that this kind of yoga therapy significantly reduce anxiety in cancer patients with mean to high effect size (d = 0.75). However, no effects significant effects were found for fatigue and depression [24]. In an observational, catamnestic study without control group based on the study above, 6 months after yoga intervention significant changes in fatigue (d = 0.32), anxiety (d = 0.33) and depression (d = 0.40) were observed compared to baseline measurement [25].

An important moderator of the effect on fatigue is frequency in exercising of the patients during and after the intervention [19, 21]. To improve exercise frequencies, participants often receive exercise CDs and/or exercise books at the end of yoga intervention [11, 16, 18–20]. Documentation of their daily exercise duration in addition to the exercise CD has also shown to be helpful for the sustainability of the effects [21]. In the area of oncological complementary therapy, supporting participants via phone calls at weekends within an ongoing mind-body intervention helps to maintain the continuity of the exercises [26]. In the medical context, daily reminder e-mails increased adherence to medication [27, 28]. However, there are no comparable studies on mind-body procedures to improve fatigue symptoms that use weekly reminder e-mails to promote sustainable effects.

In this study, the following research questions will be examined:

Primary research question:
Does an 8-week yoga intervention (IG) reduce self-reported fatigue symptoms directly after the intervention compared to a waiting-list control group (CG)? We expect an effect of d = 0.50 in favor of the IG.

Secondary research questions
2.Do gender, age, cancer, baseline fatigue, depression and period since first diagnosis moderate the effects of the yoga intervention on self-reported fatigue?3.Do reminder-e-mails after the yoga intervention reduce self-reported fatigue symptoms and improve exercise frequency compared to participants of the yoga-intervention receiving no reminder e-mails?4.Is exercise frequency associated with lower self-reported fatigue symptoms?

## Methods

The study will take place in the premises of the University Hospital Wuerzburg Radiotherapy/Palliative Care Unit. Written informed consent will be obtained from all participants. To answer the research questions, a combination of two RCTs will be implemented (see Fig. 1). In the first part, eligible patients will be randomized to the IG (8-week yoga intervention) or CG. The CG will also receive the yoga intervention, but nine weeks later than the IG. At the end of the yoga intervention, the second RCT will be implemented: all patients will be again randomized to get reminder-emails (email group) or no reminder emails after the yoga-interventions. The email group will receive a weekly email over 24 weeks a week, in which one asana out of the yoga intervention is repeated and described in detail. In addition, through the reminder-email participants will be encouraged to practice by themselves regularly. The first RCT is described in 2.1 and will be used to answer research questions 1 and 2, the second RCT is described in 2.2 and will be used to answer research questions 3 and 4.

**Fig. 1 Fig1:**
[figure not shown]
Study design; Abbreviations: IOT = interdisciplinary oncological therapy outpatient clinic; RAD = radiation therapy ambulance; R = Randomization; IG = Intervention group, CG = Control group TAU = treatment as usual

### First RCT (yoga intervention)

#### Study-setting and eligibility criteria

The participants will be at least 18 years old, will have a previous oncological disease and will undergo treatment at the radiotherapy outpatient clinic or the interdisciplinary oncological therapy outpatient clinic (IOT) at the time of screening and they report fatigue in Fischer screening (intensity ≥4, impairment ≥5). Exclusion criteria will be insufficient knowledge of German and severe emotional or physical impairment as well as more than 50 km distance to the university hospital which would require travelling.

#### Study design and measurement occasions

Eligible patients will receive the first set of questionnaires as a baseline assessment (T0). All participants will receive psychoeducation intervention (coping with fatigue). Subsequently, they will be randomized to IG or CG. The IG starts with the yoga intervention 1 week after T0, the CG starts 10 weeks after T0. The yoga intervention will be conducted for 8 weeks plus an additional lesson in the ninth week to give the participants the opportunity to catch up on a missed session. Primary and secondary outcomes will be assessed 10 weeks after the start of yoga intervention (T1) via questionnaires. Participants of the CG will also answer a questionnaire at the begin of the yoga intervention (T1) and at the end of the yoga intervention (T2, this will be used in the second RCT).

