##### Program evaluation and training time

At the end of the intervention (IG: T1; CG: T2), participants comprehensibility and applicability of the yoga theory and psychoeducation as well as subjective benefit will be assessed on a scale from 0 (not at all) to 3 (very). Furthermore, the current scope of the exercise duration (yoga) and the application frequency of the recommendations for handling fatigue will be measured at T1(IG)/T2(CG) and T3(IG and CG). Reasons for continuing or ending yoga practice are documented.

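### The primary time point T1 is dated inconsistently: read literally, week 11 after T0 in the yoga arm and week 10 in the control arm, with no rule that it precedes the e-mail randomisation

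*Protocol article*

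**What the plan says.** The dates are in the protocol article, First RCT, Study design and measurement occasions. On the start of yoga: "The IG starts with the yoga intervention 1 week after T0, the CG starts 10 weeks after T0". On its length: "The yoga intervention will be conducted for 8 weeks plus an additional lesson in the ninth week". On the outcome assessment: "Primary and secondary outcomes will be assessed 10 weeks after the start of yoga intervention (T1) via questionnaires". The next sentence gives the control arm a different anchor: "Participants of the CG will also answer a questionnaire at the begin of the yoga intervention (T1". The same sentence places CG's T2 at the end of its yoga.

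Other sections describe T1 without a week number. The primary research question in the Background asks whether yoga will "reduce self-reported fatigue symptoms directly after the intervention compared to a waiting-list control group (CG". Program evaluation and training time has "At the end of the intervention (IG: T1; CG: T2". Statistical analysis also pairs IG's T1 with CG's T2 as the fatigue value after the intervention.

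On the second trial, the Methods introduction says "At the end of the yoga intervention, the second RCT will be implemented". The Second RCT section places the allocation after yoga. Neither gives a date for the first e-mail or says that T1 must be completed beforehand.

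**The concern.** T1 fatigue is the dependent variable of the primary ANCOVA, whose only terms are treatment and baseline fatigue. If T1 lies at different distances from T0 in the two arms, any general change in fatigue during the extra week is counted as a yoga effect. An IG assessment delayed beyond the end of yoga also answers a slightly different question from the one posed, which is about the effect directly after the intervention.

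The same IG value has a second use: it is the covariate when fatigue at T3 is compared between the e-mail and no-e-mail groups. If T1 were completed after e-mails had begun, the primary contrast would include some reminder exposure in IG only. The covariate of the e-mail analysis would also be a post-randomisation measurement for those patients, and adjusting for it could remove part of the e-mail effect.

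**Working it through.** **The plan's own figures.** The stated 9-week lag between the arms ("The CG will also receive the yoga intervention, but nine weeks later than the IG") agrees with the start weeks: 10 − 1 = 9. The sample size also reproduces: for d = 0.50, two-sided alpha 0.05 and power 0.80, the two-sample t-test needs 63.77, so 64 per group, with power 0.801. Neither figure is in dispute.

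**Date of T1, in weeks after T0.** All inputs are from First RCT, Study design and measurement occasions.

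- IG: yoga start + 10 = 1 + 10 = week 11.
- CG: start of its own yoga = week 10.
- Difference: 11 − 10 = 1 week.
- Applied literally to CG, the general sentence would give 10 + 10 = week 20, which the next sentence rules out. It therefore cannot be a rule for both arms.

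**Gap between the end of yoga and IG's T1.**

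| End of IG yoga taken as | Week after T0 | Gap to week 11 | Gap to week 10 |
|---|---|---|---|
| 8 full weeks, or the ninth-week lesson if the first is at the start | 1 + 8 = 9 | 2 | 1 |
| End of the ninth week | 1 + 9 = 10 | 1 | 0 |

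The literal reading leaves 1 to 2 weeks. With weekly e-mails, that is room for one or two of the 24 before T1. CG patients cannot have had any at their T1, because they have not yet had yoga.

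**Covariate of the e-mail analysis.** IG's value is taken 10 weeks after the start of yoga. CG's T2, at the end of yoga, is about 8 to 9 weeks after its start. The paired values therefore differ by about 1 to 2 weeks in interval, although the article treats them as the same measurement.

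**Size of the one-week difference (assumption).** The article gives no rate of change. If fatigue drifts by 0.2 to 0.4 SD over 10 weeks, one week is 0.2/10 to 0.4/10 = 0.02 to 0.04 SD. That is 4% to 8% of d = 0.50. The standard error of an unadjusted standardised difference at 64 per arm is about √(2/64) = 0.18, so the bias is roughly 0.1 to 0.2 standard errors. Baseline adjustment would make the standard error somewhat smaller.

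**Size if e-mails did come first (assumption).** If they shifted fatigue by 0.05 to 0.20 SD in an assumed half of IG, the yoga contrast would move by half of that, 0.025 to 0.10 SD, or 5% to 20% of d = 0.50. The upper end is generous for one or two e-mails.

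**The case against.** The strongest reply is that one phrase is out of line and the rest of the article fits a single schedule. The research question, the program evaluation section and the statistical analysis all treat IG's T1 as the end-of-intervention value, and CG's T1 is at week 10. If the start of yoga was written where T0 was meant, T1 would be week 10 in both arms. That is plausible, but the article does not say so, and Fig. 1 is not shown, so it cannot settle the matter here. If it is a slip, the correction is the same.

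Several stronger readings might be inferred, and the reply is right to reject them:

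- **That reminder e-mails contaminate the primary endpoint.** The Methods introduction ties the end of yoga to implementing the second trial, not to sending a first e-mail, and no section dates that e-mail. The exposure is permitted, not established.
- **That control patients are already practising yoga at T1.** The text excludes this by placing CG's T1 at the start of its yoga.
- **That comparing IG after yoga with CG before yoga is itself a flaw.** That is the intended wait-list contrast.
- **That IG's T1 comes 3 weeks after the last class.** This counts from the eighth class (1 + 7 = week 8) and ignores the ninth-week lesson.

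It may also be said that the order of questionnaire and e-mail is operational detail that an article leaves to the full protocol. Taken alone, it would be. The point stands because the dates the article does state open a gap after yoga in which that order matters.

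**Conclusion.** The article contradicts itself on the date of its primary endpoint. This follows by simple addition from the stated weeks and needs no assumption. Followed literally, the arms are assessed 1 week apart, and IG's T1 falls about 1 to 2 weeks after yoga ends rather than directly after it. Reminder exposure before IG's T1 remains only a possibility, through the missing order of events.

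The severity is moderate. The 0.02 to 0.04 SD rests on an assumed drift and is small against a standard error of about 0.18 SD. A reader might conclude that the primary comparison is seriously biased; the documents do not support that. The reason to act is that questionnaires sent at the wrong time cannot be recovered, whereas the wording is easily corrected beforehand.

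**What to change.** Reconcile the passages as follows, leaving the yoga timetable as it is:

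1. Replace the definition of T1 by the start of yoga with one stated in weeks from T0, identical in both arms. Week 10 would serve, with the questionnaire completed after IG's ninth-week lesson and before CG's first class.
2. Take CG's T2 at the same interval from its yoga start as IG's T1. With T1 at week 10 that interval is 10 − 1 = 9 weeks, so T2 falls at 10 + 9 = week 19 after T0.
3. Require T1 (IG) and T2 (CG) to be completed before the second allocation is disclosed and before the first e-mail is sent.
4. Use the same description of T1 in the research question, the program evaluation section and the statistical analysis.

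The cost is protocol wording and questionnaire dispatch dates. No visits or patients are added, and the sample size and analysis model do not change.

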#### Yoga-intervention

Certified yoga teachers will carry out yoga intervention. The sequence of exercises will remain constant from beginning to end. The asanas (physical exercises from Yoga) were inspired by John-Kabat Zinn and adopted for cancer patients by [name] (psychooncologist, physiotherapist and yoga teacher). One yoga session will last 1 hour. It consists of physical exercises (asanas), conscious breathing (Pranayama) and deep relaxation (Savasana). Nonviolence (ahimsa) as an important basic principle of yoga is to be repeated every hour and helps to encourage the participants to deal gently with their bodies. Participants should not perform any physical exercises that cause pain. The subsequent body exercises are structured from lying to sitting to standing. The following sequence of exercises will be repeated in each yoga unit: 1) Relaxation: conscious breathing, body scan, mindfulness 2) Vein pump 3) Pelvis and back rotation (adapted variation of the “nakrasana”) 4) Pelvis opening (adapted variation of the “supta baddha konasana”) 5) Shoulder bridge (“setu bandha sarvangasana”) 6) Forward folds (Paschimottanasana and variations with Pranayama) 7) Backbend: intense east stretch (Purvottasana) 8) Diagonal static yoga cat (Majariasana 1 and resting pose) 9) Standing exercise 10) Upward Salute(Urdhva Hastasana) 11) Warrior 1 (Virabhadrasana 1) 12) Warrior 3 (Virabhadrasana 3) 13) Tree (Vrkasana variation) 14) Relaxation (Savasana). In all exercises, participants are reminded to breathe slowly, deeply and consciously. Adverse events and complications during yoga therapry are recorded by yoga teachers on a standardized basis.

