### Second RCT (reminder e-mails)

#### Study design and measurement occasions

After the yoga intervention, all participants are randomly assigned to group “Email” who will get weekly reminder e-mail or to group “NoEmail” who will receive no reminder e-mails. Participants of both groups will receive a practice book and a practice CD. Outcomes will be assessed 6 months after the end of the yoga therapy (T3).

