#### Reminder e-mail

Reminder e-mails are used for the second question. The e-mails in the first 12 weeks contain descriptions of the twelve asanas - one asana each week - and an encouragement to practice yoga during this week. The asanas are described analogously to the order of the yoga classes. In the following 12 weeks, the 12 reminder e-mails will be repeated in the same order.

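### The only adverse-event recording described is by yoga teachers during yoga therapy, so event rates cannot be compared between the randomised groups at T1 or T3

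*Protocol article*

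**What the plan says.** The Yoga-intervention section of the first RCT holds the article's only sentence on adverse events: "Adverse events and complications during yoga therapry are recorded by yoga teachers on a standardized basis".

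The teacher-led period is short. Under Study design and measurement occasions (first RCT), "The yoga intervention will be conducted for 8 weeks plus an additional lesson in the ninth week". The arms are staggered: "The IG starts with the yoga intervention 1 week after T0, the CG starts 10 weeks after T0". No teacher contact is described for the control group (CG) before its course begins.

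After the course the trial moves to practice without a teacher. In the second RCT, "Participants of both groups will receive a practice book and a practice CD". For the e-mail group, the Methods introduction adds that "through the reminder-email participants will be encouraged to practice by themselves regularly". Under Reminder e-mail, twelve weekly messages each describe one asana, and then "In the following 12 weeks, the 12 reminder e-mails will be repeated in the same order". T3 falls 6 months after the end of yoga therapy.

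Some related data are collected. The outcomes sections list ESAS (including pain, shortness of breath and general condition) and QLQ-C15-PAL (including pain and physical function), by default at every measurement time. Use of analgesics and psychopharmaceuticals is recorded at each occasion. The programme evaluation documents why patients continue or end yoga practice.

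**The concern.** A trial supports a statement about harm in the same way as one about benefit: the same question is put to both randomised groups over the same window. Here benefit is measured that way in both RCTs. Adverse events, as described, are collected only through the person delivering the intervention, while it is being delivered.

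Three gaps follow.

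- **Waiting control group.** T0 to T1 is the only randomised window of yoga against no yoga. Patients are under treatment in an oncology outpatient clinic at screening, so background events are to be expected. Without a comparable CG count, events in the intervention group (IG) cannot be set against that background.
- **Home practice.** The second RCT tests prompts to practise alone, and no adverse-event collection is described for those months.
- **Non-attenders.** A patient who stops coming because of a problem leaves the recorder's view.

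This matters because the Discussion says that, if yoga reduces fatigue, it should enter routine practice. If the e-mails help, it foresees internet-based sessions or independent practice at home. That last mode is the one with no described event recording.

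**Working it through.** The article states no figure on this point, so there is none to reproduce. The check sets the recording window against the trial timeline.

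**Inputs, all from the article**
- Teacher-led course: 8 weekly sessions plus a catch-up lesson in week 9, so at most 9 weeks.
- E-mail phase: 12 + 12 = 24 weeks.
- CG course start: 10 weeks after T0.
- T3: 6 months after the course, taken as about 26 weeks.

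**Step 1: e-mail participant, course plus e-mail phase.** Share of weeks outside the described recording = 24 / (9 + 24) = 24/33 = 0.727, about 73%. Counting only the 8 scheduled weeks gives 24/32 = 75%. Taking the full 6 months to T3 gives 26 / (9 + 26) = 26/35 = 74%, and this last figure applies to the NoEmail group as well. These are shares of calendar time. They are not shares of practice time or of missed events.

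**Step 2: CG before T1.** The wait runs from T0 to week 10. No part of it falls within yoga therapy, so the described recording gives no CG event count to set beside the IG count. During its own later course the CG comes under the same teacher recording, but by then there is no untreated comparator.

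**Step 3: what the other data can show**

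| Source | Groups and times | What it gives | What it lacks |
|---|---|---|---|
| ESAS, QLQ-C15-PAL | all groups, T0 to T3 | level of pain, breathlessness, function | falls, injuries, care sought, link to yoga |
| Analgesic use | each occasion | indirect sign of pain | cause or event |
| Reasons for continuing or ending practice | programme evaluation | harm in some patients who stop | a CG patient still waiting; a count of events in those who continue |

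None of these is an adverse-event count that can be compared between groups.

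**Step 4: what home practice contains.** The e-mails cover twelve asanas in class order. The Yoga-intervention list has 14 elements, of which 12 lie between the opening and closing relaxation. The e-mailed set therefore probably includes the shoulder bridge, the backbend, Warrior 3 and Tree. This is an inference, as the article does not list the e-mailed asanas.

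**The case against.** The strongest objection is that exclusivity is read from silence. The sentence does not say that nobody else records events, and a condensed article may leave safety procedures to a fuller document. This stands in part, so the point is limited to what is described. Against it, the sentence fixes a recorder and a window, and the ethics section says that the paper contains the original study protocol.

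Second, the article elsewhere uses yoga therapy for the whole 8-week course. Attenders could then report a problem felt after a class, or at home between classes, at the next session. That is a fair reading. It narrows the gap during the course but does not reach the CG's wait, the months after the course, or patients who no longer attend.

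Third, the risk should not be overdrawn. The exercises were adapted for cancer patients, participants are told not to do anything that causes pain, and severe physical impairment is an exclusion.

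Three stronger readings are tempting but unsupported:
- A reader might infer that the CG provides no harm information at T1, or that no randomised comparison bearing on harm is possible. Pain scores and analgesic use are collected in both arms and can be compared. What is missing is a comparable event count.
- A reader might infer that harms in home practice have no route at all into the data. The documented reasons for ending practice are a partial route.
- A reader might convert the gap into a share of practice hours. The article gives no expected home-practice time, so such a figure would rest wholly on assumed minutes per week.

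**Conclusion.** The point holds as a limited one. The adverse-event recording described covers the teacher-led course. It yields no comparable count for the CG between T0 and T1, and none is described for the 6-month home-practice phase or for patients who stop attending. Event rates therefore cannot be compared IG versus CG at T1 or Email versus NoEmail at T3. About 73% of an e-mail participant's course-plus-e-mail weeks lie outside the described recording (73% to 75% across the ways of counting shown).

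This assumes that no other adverse-event procedure exists outside the article. If one does, the remedy is to describe it. The sample size, the primary fatigue analysis and the four research questions are not affected. What is limited is how far the results can support the routine and home use that the Discussion foresees.

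**What to change.** Add one short harms item, worded identically for all groups, to the existing T1, T2 and T3 questionnaires. It should ask about any fall, injury, or new or worse problem since the last questionnaire, whether the patient sees a link to yoga, and whether medical care was sought. Send it also to patients who have stopped attending. Report it descriptively, IG versus CG at T1 and Email versus NoEmail at T3, separately from the teacher log. State in the protocol whether the teacher log covers the session only or the whole course.

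The comparison should stay descriptive. Even with no events among 64 patients, the one-sided 95% upper limit for the event rate is 1 − 0.05^(1/64) = 4.6%.

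The cost is a slight added burden on forms that patients already complete, with no new visits. The answers will be unblinded self-report, and recall to T3 spans about 6 months, so they complement the teacher log and do not replace it.
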